### Sample size calculation

The sample size needed for evaluating participant acceptability is based on the proportion of participants who showed an increase in enablement, measured by the Patient Enablement Instrument (PEI), one year after enrolment into the CDCC Pilot Scheme. Previous studies showed that 55.6–72.2% of participants reported PEI score > 0 after entering structured programmes for DM and/or HT [10–12]. Assuming the proportion of CDCC participants with PEI score > 0 at 12 months to be 50%, 383 CDCC participants are required with 5% margin of error and significance level of 5%. To allow for about 30% attrition, the sample size required will be 548.

The sample size for evaluating the effectiveness and cost-effectiveness was determined based on the difference in the proportion of patients achieving the targeted outcome for disease control after 12 months between CDCC participants and the comparison group. Previous studies evaluating the 12-month effectiveness of the multi-disciplinary Risk Assessment and Management Program for DM or HT implemented in public primary care in Hong Kong found that the proportion of participants achieving treatment target (glycated hemoglobin [HbA1c] < 7.0% or systolic/diastolic blood pressure [BP] < 140/90mmHg) increased by 5.40% [13] or 1.18% [14], respectively after 12 months, compared to patients receiving usual care. Assuming a conservative 3% increase in the proportion of participants achieving treatment target after 12 months in the CDCC group, a total of 378 participants with pre-DM, HT and/or DM are required to detect difference at a power of 80% with a significance level of 5%/ According to the Hong Kong Population Health Survey 2020, the prevalence of undiagnosed HT and DM among individuals aged 45–84 was 15.4% and 4.6%, respectively [15]. Previous studies reported that the prevalence of pre-DM was 2.3–8.9% in Hong Kong [15, 16]. Taking a prevalence of approximately 20% in total for pre-DM, HT and/or DM, and accounting for an attrition of 30%, a total of 1,886 non CDCC participants will be required.

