### Data analysis

The proportion of patients and/or service providers achieving the standards of care, participant experience, satisfaction and enablement, and the costs of the CDCC Pilot Scheme and the direct medical costs from the participants at 12 months will be described with descriptive statistics. Differences in the proportion of participants reaching the targeted disease control outcomes between CDCC and non-CDCC participants will be compared using chi-squared tests, and adjusted for confounding factors by logistic regression. Changes in clinical parameters from baseline to 12 months will be compared between CDCC and non-CDCC participants by paired t-tests. The total mean costs on each CDCC and non-CDCC participant will be compared using t-tests. The additional costs required for an additional participant in the CDCC Pilot Scheme to achieve target outcomes of disease control after 12 months will be reported as the ICER, calculated as the incremental cost incurred for each participant of the CDCC Pilot Scheme divided by the difference in the proportion of participants meeting targeted disease outcome. Cost-effectiveness of the Scheme would be determined by comparing the ICER to the willing-to-pay threshold of 1 GDP per year.

All statistical analyses will be performed using Stata (version 15.1). A p-value < 0.05 is considered statistically significant.

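### The stated 80% power for a 3-point difference with a total of 378 participants cannot be reproduced at any realistic comparison-group rate, and the analysed numbers give far less.

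*Protocol article*

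**What the plan says.** The Sample size calculation section of the protocol article bases the effectiveness calculation on a contrast of CDCC with non-CDCC participants: "based on the difference in the proportion of patients achieving the targeted outcome for disease control after 12 months between CDCC participants and the comparison". The effect size comes from two earlier programme evaluations, one in diabetes and one in hypertension, whose results are given only as differences: proportions at target "increased by 5.40% [13] or 1.18% [14], respectively after 12 months, compared to patients receiving usual care". The plan takes a value between the two: "Assuming a conservative 3% increase in the proportion of participants achieving treatment target after 12 months in the CDCC group". For that effect it names its requirement at the 5% significance level, namely that "a total of 378 participants with pre-DM, HT and/or DM are required to detect difference at a power of 80" per cent. It then applies a prevalence of about 20% and attrition of 30% to reach 1,886 non-CDCC recruits.

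The Data analysis section says that proportions at target "between CDCC and non-CDCC participants will be compared using chi-squared tests, and adjusted for confounding factors by logistic regression", with the rule that "A p-value < 0.05 is considered statistically significant". The Outcome measures section lists this difference as a primary outcome. Success means BP below 140/90 in hypertension, HbA1c below 7% in diabetes, or any fall in HbA1c in pre-diabetes. The Subjects section takes the CDCC group from records in an enrolment window and gives no number.

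**The concern.** The sample size for a difference of two proportions depends heavily on the comparison-group proportion, and none is stated. For a difference as small as 3 points, a few hundred participants suffice only when one group sits almost at 0% or 100%. The targets make such a rate unlikely, because any fall in HbA1c counts as success in pre-diabetes, and some people with newly detected disease will meet a BP or HbA1c threshold whatever care they receive.

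This contrast is the fourth hypothesis and supplies the denominator of the ICER. If the published 80% is taken at face value, a non-significant result could be mistaken for evidence against a 3-point benefit that the study had little chance of detecting.

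**Working it through.** **Inputs.** From Sample size calculation: difference d = 0.03 (read as absolute), power 80%, alpha 5%, total 378, prevalence 0.20, attrition 0.30, 1,886 recruits. From Data analysis: chi-squared test between independent groups. Assumed here because not stated: two-sided test, comparison rate p1 (scanned), CDCC group size (equal or very large).

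**Formula.** With p2 = p1 + 0.03 and p̄ their mean, n per group = [1.960·√(2p̄(1−p̄)) + 0.842·√(p1(1−p1) + p2(1−p2))]² / 0.03².

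**Trying to reproduce 378.**
- *As a total.* The smallest case at equal allocation is 0% against 3%: (0.3369 + 0.1436)²/0.0009 = 256.5, so 257 per group or 514 in total. Optimising the allocation as well brings the minimum to 486 (one-sided: about 390). No rate gives 378.
- *As 378 per group.* At p1 = 0.72%: (0.4084 + 0.1744)²/0.0009 = 377.4, so 378. The mirror case is about 96.3% against 99.3%.
- *From the recruitment figure.* 264/0.70 = 377.1, rounded up to 378, and 264/(0.20 × 0.70) = 1,885.7, rounded up to 1,886. By contrast 378/(0.20 × 0.70) = 2,700. So 378 seems to include attrition already, with 264 analysed. At 264 per group the formula needs p1 of about 0.04%, or the mirror near 97%.

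**Check at the boundary.** The normal approximation is rough near 0%, so I also enumerated the uncorrected chi-squared test exactly. With 189 per group and 0% in the comparison group, significance needs at least 4 successes among 189 CDCC participants (4 v 0 gives chi-squared 4.04; 3 v 0 gives 3.02). The chance of that at 3% is 82%. At 0.1% against 3.1% power is already down to 76%. With 264 and 378 per group, exact power falls to 80% at about 0.3% and just under 1%. The boundary moves by a fraction of a point, and the conclusion is the same.

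**What 3 points would need** (per group, equal allocation): 1,774 at a comparison rate of 10%, 3,763 at 30%, 4,356 at 50%, 3,554 at 70%, 1,356 at 90%. For 50%: (1.3853 + 0.5946)²/0.0009 = 4,355.4.

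**Power for 3 points.** Power = Φ[(0.03 − 1.96·SE0)/SE1], with SE0 pooled and SE1 unpooled. For 264 per group at 50%: SE0 = 0.04350, SE1 = 0.04348, so Φ(−1.27) = 10%.

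| Analysed comparators | Rates 30–70%, equal groups | Rates 30–70%, very large CDCC group | Highest over 10–80%, very large CDCC group | Rate 90%, very large CDCC group |
|---|---|---|---|---|
| 189 (378 in total) | 8–9% | – | – | – |
| 264 | 10–12% | 16–20% | 28% | 48% |
| 378 | 13–15% | 21–27% | 40% | 61% |

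**What 264 comparators can show at rates of 30–70%.** The difference detectable with 80% power is about 10.5–12 points with equal groups and about 7.5–8.6 points with a very large CDCC group. The 95% interval half-width runs from 1.96·√(0.21/264) = 5.5 points (very large CDCC group, rate 30% or 70%) to 1.96 × 0.04348 = 8.5 points (equal groups, rate 50%).

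**The case against.** The strongest reply is that the CDCC group comes from records and may be much larger than the comparison group. That stands and is why the table has the large-group columns. It helps, but over rates of 10–80% it does not lift power above about 28% (264 comparators) or 40% (378). Only near the ceiling does it rescue the claim: at a comparison rate of 95% with a very large CDCC group, power passes 80%. The document does not suggest such a rate.

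Other readings do not help. One-sided testing with 378 per group still needs a rate of about 1.3% or lower (or its mirror near the ceiling), and a relative 3% increase needs far larger numbers except at rates around 96–97%.

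Nor is this only a detail that a journal article omits. The same section states the assumed proportion (50%) for the enablement calculation, and here a definite power figure is published.

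Three stronger readings are tempting and not supported:
- A reader might quote one figure, such as 11–25%, as the study's true power. No comparison rate and no CDCC group size are given, so any figure is conditional.
- A reader might weight the two cited effects by the hypertension and diabetes prevalences and conclude that about 2.15% was to be expected. The analysed population includes pre-diabetes, which has its own target and no cited effect, so no weighted effect can be computed.
- A reader might call 3% an arithmetic error. It lies between the cited 1.18% and 5.40% and just below their midpoint of 3.29%. What is unsupported is only calling it conservative, since it is more than double the hypertension effect.

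The ICER can still be calculated from the observed difference. Low power makes it imprecise, not impossible.

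**Conclusion.** The power statement is wrong as written. With the standard formula no comparison rate or allocation makes a total of 378 sufficient, and exact calculation rescues it only at essentially 0% or its mirror at 97%. The per-group readings (378, or the 264 implied by 1,886) also need rates at one extreme, which fit poorly with the study's own targets.

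The size of the shortfall depends on the assumed comparison rate of 30–70%, a two-sided 5% test and an absolute 3-point difference. On those terms power is about 8–15% for equal groups of 189 to 378, and at most about 20% or 27% with 264 or 378 comparators and a very large CDCC group. It is higher at more extreme rates. The finding that 3 points is well beyond reach at mid-range rates does not depend on how 378 is read.

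**What to change.** Replace the power sentence with one that gives the assumed comparison-group proportion (or a range), the sidedness, the analysed number in each group and the allocation. It should also say whether 378 is a total or per group, and before or after attrition. Then restate either the power for 3 points or the difference detectable with 80% power, and add the expected confidence-interval half-width. With 264 analysed comparators and rates of 30–70% these would be about 7.5–12 points and about 5.5–8.5 points, depending on the CDCC group size. Justify the word conservative against the cited 1.18%, or remove it. Report the result for the fourth hypothesis with its confidence interval.

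The cost is a rewritten paragraph. No extra enrolment is asked for. The downside is that the stated power for 3 points becomes much less favourable.

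### The comparison-group sample size does not chain: 378 participants, 20% prevalence and 30% attrition give 2,700, not 1,886, so it is unclear which number carries the 80% power

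*Protocol article*

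**What the plan says.** The second paragraph of Sample size calculation (protocol article, Methods) sizes the effectiveness and cost-effectiveness comparison. The effect is set by "Assuming a conservative 3% increase in the proportion of participants achieving treatment target after 12 months in the CDCC group". The paragraph then says that "a total of 378 participants with pre-DM, HT and/or DM are required to detect difference"; it sets power at 80% and significance at 5%.

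Two inflation steps follow that number. The first is "Taking a prevalence of approximately 20% in total for pre-DM, HT and/or DM". The second comes with the result: "accounting for an attrition of 30%, a total of 1,886 non CDCC participants will be required".

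The first paragraph of the same section sizes the acceptability survey. There, 383 participants are needed for the stated precision, and an allowance of about 30% attrition brings this to 548.

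**The concern.** As worded, 378 is the number of people with a diagnosis who are needed for the test, and both inflations come after it. A reader who applies them does not arrive at 1,886. In addition, 378 is called a total for a two-group comparison, yet it is converted entirely into non-CDCC recruits.

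This paragraph supports the between-group difference in disease control at 12 months, which is listed under primary outcomes. Under Data analysis the same difference is the denominator of the ICER. The Discussion says that recruitment of the comparison group is under way, so 1,886 is a working target. If the power belongs to 378, the target is too small for the claim made; if it belongs to a smaller number, the sentence about power is wrong. Either way, the number analysed cannot later be judged against the plan.

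**Working it through.** **Inputs, all from Sample size calculation:** 378 diagnosed participants required; prevalence 20%; attrition 30%; stated result 1,886 non-CDCC participants.

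**The article's own attrition convention.** 383/(1 − 0.30) = 547.1, rounded up to 548. The number tied to precision is divided by 0.70.

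**The chain as written.** 378/0.20 = 1,890 to be screened before attrition, and 1,890/0.70 = 2,700. The stated 1,886 is 814 lower (814/2,700 = 30%).

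**Other readings:**

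| Reading | Arithmetic | Result |
|---|---|---|
| Attrition as a 30% add-on | 378/0.20 × 1.30 | 2,457 |
| 378 covers both groups, 189 each | 189/0.20/0.70 | 1,350 |
| Same, with a 30% add-on | 189/0.20 × 1.30 | 1,229 |
| Prevalence only, no attrition after 378 | 378/0.20 | 1,890 |
| 378 already contains attrition | 264/0.70 = 377.1 → 378; 264/0.70/0.20 = 1,885.7 | 1,886 |

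Only the last two land at or near 1,886, and the last gives both printed figures exactly. In neither is attrition applied on top of 378.

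**What 1,886 yields at the planning values.** 1,886 × 0.20 = 377 diagnosed at baseline; × 0.70 = 264 analysable at 12 months.

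**Consequence if 378 analysed comparators are needed.** 378 − 264 = 114 short (114/378 = 30%). Suppose 378 per group does give 80% power, two-sided at 5%, so that the expected test statistic is 1.96 + 0.84 = 2.80.
- 264 comparators against 378 CDCC participants: the variance rises by (1/264 + 1/378)/(2/378) = 1.216, the statistic falls to 2.80/√1.216 = 2.54, and power is about 72%.
- 264 in both groups: 2.80 × √(264/378) = 2.34, and power is about 65%.

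These two figures scale from the article's 80%; they do not confirm it.

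**Consequence if 264 are needed.** 1,886 × 0.20 × 0.70 = 264, so there is no shortfall. The error is that power is attached to 378.

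**The case against.** The strongest defence is that nothing is wrong with 1,886. Because 264 reproduces both printed figures, 378 is plausibly the number after attrition and only its label slipped. A reader might infer from the printed chain that 2,700 recruits are required, or that the study will be 114 cases short. The documents do not support either as a firm conclusion. Both need 378 to be the number before attrition and to consist of comparators only, and the text establishes neither. If 378 were a total for two equal groups, 189 comparators would be needed and 264 would exceed that. This part of the defence stands.

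A second defence concerns prevalence. The article reports that "the prevalence of undiagnosed HT and DM among individuals aged 45–84 was 15.4% and 4.6%, respectively", which already sums to 20.0%, and it quotes 2.3–8.9% for pre-DM. Without overlap the total is 22.3–28.9%, and 1,886 recruits would yield 1,886 × 0.223 × 0.70 = 294 to 1,886 × 0.289 × 0.70 = 382 analysed cases. The top of that range would meet 378. So 264 is the yield at the planning prevalence and not a forecast. This does not repair the calculation, because the text states that about 20% was used and overlap between conditions would lower the range.

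The back-calculation to 264 is also only an inference. The comparator rate is not given, so neither 264 nor 378 can be tied to a 3-point difference. Whether either number suits that difference is a separate question.

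The article format is no answer here. The inputs and the result are both printed, and they disagree.

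**Conclusion.** The paragraph is internally inconsistent and needs correction. On its own inputs the chain gives 2,700, against 1,886 stated. None of the readings tried makes 378, about 20% prevalence and a further 30% attrition produce 1,886.

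The size of the consequence is conditional. If 378 is the analysed comparator number, the planned recruitment is 114 (30%) short at the planning values, and power falls to roughly 65–72% if 80% was correct for 378 per group. If 264 is the powered number, the recruitment target stands and the fault is a mislabelled figure. The exact match to 264 makes the second reading plausible, but only the sponsor's calculation can settle it.

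**What to change.** The sponsor should establish from its own calculation which number carries the 80% power and whether that number is per group or a total. The paragraph should then run in one direction: analysed at 12 months, identified with a diagnosis at baseline, screened.

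- **If 264 is the powered number:** write 264 analysed comparison participants with pre-DM, HT and/or DM, 378 identified at baseline to allow for 30% attrition, and 1,886 screened at 20% prevalence. Attach the 80% to 264.
- **If 378 is the powered number:** keep 1,886 and restate the power or the detectable difference at about 264 analysed comparators.
- **If 378 is a total for both groups:** state the split and rebuild the chain from the comparison group's share.

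In every case, state the comparator rate used and give the expected CDCC group number separately.

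The cost is a rewritten paragraph. Recruitment need not change under the first two options. The drawback is that the stated power may become less favourable.

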### Data collection

#### Evaluation of the quality of care

The CDCC Pilot Scheme will be evaluated based on a systematic and user-centric approach described by Donabedian et al. [17], where components of the programme are classified into a taxonomy of structure, process and outcome of quality of care. Structure refers to the conditions which care is provided including infrastructure (facilities and equipment), human resources, staff training and organizational characteristics. Process refers to the set of activities that go on within and between healthcare providers and patients, i.e., the provision of diagnosis, treatment, prevention, and education etc. Outcomes refer to the changes in patients’ health that can be attributed to healthcare, and may include changes in health status, patient knowledge, behavior and patient satisfaction.

Evidence-based quality of care indicators and standards on the structure, processes and outcomes will be established based on the operation protocols developed by the Primary Healthcare Commission, and in consultation with the service providers. The evaluation framework is attached in Appendix A. Site visits at DHC/DHC Express by the research team were carried out between June and August 2024 to understand the programme operation. A site visit form with a standardized flow and questions asked during the site visit was developed to ensure consistency in data collection. Data on the structure of care are collected through questionnaires completed by the operation managers at DHC/DHC Express at 6 and 12 months, and by a representative sample of FDs and allied health professionals at 12 months. Data on the process and outcomes of care will be extracted from eHealth and DHC IT module. Compliance to standards of care across different service providers will be measured based on the evaluation framework.

#### Evaluation of the effectiveness and cost-effectiveness

Anonymous data including demographics, diagnoses, prescriptions and laboratory tests (e.g. full lipid profile and renal function test) at baseline and 12 months for CDCC participants will be extracted from the eHealth database and DHC IT module, whereas those for non-CDCC participants will be collected via a telephone survey by an independent professional survey provider, and they will complete the screening blood test at a designated laboratory. With the exception of critical results that requires immediate medical attention, participants of the comparison group will be asked to follow up on any abnormal results on their own.

Costs of the CDCC Pilot Scheme composes the of implementation and operation costs by health service providers and the direct medical costs of participants. The total costs of implementing CDCC services will include all expenditure incurred from setting up the programme until 31 Dec 2024, while ongoing operational costs would be collected over a 1-year period from Dec 2023– Dec 2024 (Appendix C). Costs will be collected from each DHC/DHC Express, a representative sample of service providers and the Primary Healthcare Commission at 12 months using a costing questionnaire.

Direct medical costs refer to the ongoing costs on utilization of public and private healthcare services (including hospitalization, Accident & Emergency department, General Out-patient Clinics, and Specialist Out-patient Clinics) for both CDCC and non-CDCC participants, as well as the co-payment for the CDCC services among CDCC participants, within 12 months from enrolment. The information will be extracted anonymously from the Hospital Authority’s eHealth database and Clinical Management System, and collected from participants through telephone survey at 12 months (Appendix D). The cost of public healthcare service utilization will be estimated by multiplying the frequency of utilization with the unit cost published in the Gazette and Hospital Authority ordinance (Chap. 113) of charges for non-entitled persons for each public healthcare service.

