## Background

The Hong Kong public healthcare system is faced with ever-increasing challenges brought about by an aging population, greater prevalence of chronic diseases, rising costs of medical care, as well as increased citizen expectations from health systems. Reconfiguration of the primary healthcare (PHC) system to a preventive-oriented system equipped with multi-disciplinary teams could enable healthcare systems to be more effective and efficient. There is compelling international evidence suggesting that having a family doctor (FD) as a regular source of primary care is associated with significantly lower odds of avoidable hospitalization in chronic disease patients [1–3], as well as improved patient outcomes [4, 5].

To alleviate the growing burden placed by chronic diseases on the public healthcare system, the Hong Kong government has developed the Primary Healthcare Blueprint outlining strategies to strengthen district-based primary care services across Hong Kong. Among these strategies include the early identification and intervention of chronic diseases through disease screening at the community level, streamlining the referral system, and engaging the private healthcare sector to improve accessibility to quality PHC.

Specifically, the Chronic Disease Co-Care (CDCC) Pilot Scheme was launched in November 2023 to provide targeted subsidy for the screening and management of hypertension (HT), diabetes mellitus (DM) and pre-diabetes (pre-DM) in the private healthcare sector. Studies have found that screening adults for DM and pre-DM is cost-saving from a health system’s perspective and can lower pre-mature mortality rates [6, 7]. In addition, concurrent screening and management of HT and DM with a multi-disciplinary intervention has been shown to be cost-saving in part because of the reduction in complications and subsequent utilization of public secondary and tertiary health services [8, 9].

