## Methods

### Study design

This study consists of three parts. First, the evaluation of the quality of care is a cross-sectional study including site visits at DHC/DHC Express, administration of two serial quality of care questionnaires at 6 and 12 months among service providers, and extraction of the Scheme operational data from the eHealth database and DHC IT module, which are electronic databases used by the DHC/DHC Express to record participant data. Second, the evaluation of participant acceptability is a longitudinal cohort study by telephone surveys among CDCC participants at 3 and 12 months after CDCC enrolment. Third, the evaluation of the effectiveness and cost-effectiveness is a 1-year comparative cohort study using longitudinal data on health outcomes and healthcare utilization (and hence direct medical costs) among CDCC and non-CDCC participants at baseline and 12 months. Costing questionnaires on the set-up and operation costs of the Scheme will be distributed among service providers.

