### Subjects

To evaluate the quality of care, all operators of the DHC/DHC Express, and selected FDs and allied health professionals, will be asked to complete quality of care questionnaires. All participants who have enrolled into the CDCC Pilot Scheme between 1 Jan and 30 Jun 2024 will be included in the evaluation of the standards on process and outcome of care.

A convenient sample of 548 CDCC participants would be recruited from all 18 DHC/DHC Express between 1 Apr 2024 and 31 Aug 2024 to complete a survey on self-reported outcomes on participant acceptability and enablement. A conservative target of 140 participants for each diagnosis (i.e., normal, pre-DM, HT and DM) will be set to ensure different patients are equally represented.

The effectiveness and cost-effectiveness of the Scheme will be evaluated by comparing the differences in health outcomes and healthcare utilization rates among CDCC and non-CDCC participants at 12 months after enrolment. Records for CDCC participants enrolled between 1 Jan and 30 Apr 2024 who meet the inclusion criteria to participate in the CDCC Pilot Scheme will be included as the intervention group, while participants in the comparison group would be non-CDCC participants recruited in the community through collaboration with local networks and organizations. Participants ≥ 45 years, without a known diagnosis of HT and/or DM, and provide informed consent are eligible to join the study.

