## Discussion

The CDCC Pilot Scheme is a territory-wide programme to advocate early screening and management of chronic diseases with private-public partnership in the community setting. The implementation of the Scheme involves various stakeholders including the Primary Healthcare Commission, DHC/DHC Express, FDs and allied health professionals. A timely evaluation of the Scheme at this pilot stage is needed to assure the cross-sector collaboration works as expected and to inform strategies for quality enhancement in the future. Guided by the three domains of quality of care (structure, process and outcome), key stakeholders were involved at the initial phase to develop the evaluation criteria and standards, incorporating feedback from service providers based on real-world practice. The inclusion of various stakeholders and providers, and adoption of both subjective (self-reported outcomes) and objective (site visits and health parameters) data collection methods enhance the validity and reliability of the results. Results of the evaluation could shed light on good practices that has already been adopted and inform future guidelines to improve service quality.

Previous evaluation studies on the Risk Assessment and Management Program in Hong Kong, a chronic disease management programme implemented in public primary care, discussed approaches to facilitate the evaluation of multi-disciplinary programme [26]. They include coordinating stakeholder collaboration and communication, continuous feedback and planning meetings, stakeholder endorsement and validation, development of evaluation framework and operation definitions, and ensuring data quality. These recommendations have been incorporated in the current evaluation.

The CDCC Pilot Scheme was officially launched in the November 2023. To date, the evaluation framework has been developed, and have already conducted all site visits to DHC/DHC Express. The recruitment of participants for the participant experience and enablement survey and control group non-participants are in progress. We anticipate the major challenges in the evaluation to be:

Stakeholder endorsement and validation.

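### A comparator who joins the CDCC Scheme during follow-up adds its benefit, but not its co-payment, to the comparison group; joining should be recorded and costed by actual use.

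*Protocol article*

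**What the plan says.** - **Design** (Protocol article, Study design). The third part of the study is "a 1-year comparative cohort study using longitudinal data on health outcomes and healthcare utilization", with measurements at baseline and 12 months.
- **Who the comparators are** (Subjects). The text says "participants in the comparison group would be non-CDCC participants recruited in the community through collaboration with local networks and organizations". One eligibility statement is given: "Participants ≥ 45 years, without a known diagnosis of HT and/or DM, and provide informed consent are eligible to join the study". It sets no condition about joining the Scheme later.
- **What the study does to them** (Evaluation of the effectiveness and cost-effectiveness). Of the comparators it says "they will complete the screening blood test at a designated laboratory" and, except for critical results, "participants of the comparison group will be asked to follow up on any abnormal results on their own". That request implies that they learn their results.
- **What else is available to them** (Discussion). "The CDCC Pilot Scheme is a territory-wide programme to advocate early screening and management of chronic diseases". The Background dates the launch to November 2023. The secondary outcomes put the pilot phase at 1–2 years.
- **Costs** (Evaluation of the effectiveness and cost-effectiveness). Use of public and private services is counted in both groups. The Scheme co-payment is counted by group: "as well as the co-payment for the CDCC services among CDCC participants, within 12 months from enrolment". Implementation and operating costs are collected from providers and the commissioning body up to December 2024. How they are divided per participant is not stated.

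**The concern.** The study itself prompts comparators with abnormal results to seek care. These are the people in whom target attainment is assessed. For someone aged 45 or over with a newly found abnormal result, a subsidised programme for that condition is an obvious place to go. Comparator recruitment was still under way when the article was written, after the June–August 2024 site visits, so at least part of comparator follow-up overlaps with a running Scheme.

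A comparator who joins receives Scheme care, which narrows the contrast in target attainment. The co-payment rule, however, follows the group label and not the service used. The ICER divides incremental cost by the difference in attainment. Crossover therefore shrinks the denominator, while the numerator does not shrink with it if the joiner's Scheme cost is left out. Two primary outcomes are affected: the difference in target attainment and the ICER. The second is compared with a willingness-to-pay threshold.

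An analyst cannot repair this afterwards if Scheme enrolment among comparators was never recorded.

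**Working it through.** **The plan's own figures.** Sample size calculation uses a 3-point difference, 378 people with a diagnosis, 20% prevalence, 30% attrition and 1,886 comparators. The last step can be traced: 264 / 0.7 = 377.1 (378), and 264 / 0.2 / 0.7 = 1,885.7 (1,886). So 378 appears to include attrition already, and the chain allows for prevalence and attrition but not for crossover. The 378 itself is not reproduced as a two-arm total for a 3-point difference. At two-sided 5% and 80% power, the number per arm is 4,356 at a 50% comparator rate and 1,356 at 90%; no comparator rate is stated. That is a separate matter, and only the 3-point difference is used below.

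**Symbols.**
- c: share of diagnosed comparators who join the Scheme. Not in the article; 10–30% is assumed.
- D = 3 points: planned difference.
- ΔC: incremental cost per CDCC participant without crossover.
- k: share of ΔC that is not recorded for a joiner. Not in the article; 0 to 1 is shown.

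**Formulas**, with joiners gaining the full benefit and otherwise costing the same as CDCC participants:
- Observed difference = D(1 − c).
- Power of a design with a true 80% = Φ[(1.96 + 0.84)(1 − c) − 1.96].
- Observed incremental cost = ΔC[1 − c(1 − k)].
- ICER multiplier = [1 − c(1 − k)] / (1 − c). This is 1/(1 − c) when k = 1, and 1 when k = 0.

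| c | Difference (points) | Power, if nominally 80% | ICER × (k = 1) | ICER × (k = 0.5) | ICER × (k = 0) |
|---|---|---|---|---|---|
| 0.10 | 2.7 | 71% | 1.11 | 1.06 | 1.00 |
| 0.20 | 2.4 | 61% | 1.25 | 1.13 | 1.00 |
| 0.30 | 2.1 | 50% | 1.43 | 1.21 | 1.00 |

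Worked line for c = 0.20: the difference is 3 × 0.80 = 2.4. The multipliers are 1/0.80 = 1.25, 0.90/0.80 = 1.125 and 0.80/0.80 = 1.

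**Partial benefit.** If joiners gain only a fraction b of the benefit, the difference is D(1 − bc). With b = 0.5 and c = 0.20 it is 3 × 0.90 = 2.7 points, and the k = 1 multiplier is 1/0.90 = 1.11.

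**What the two parts show.** Dilution of the difference follows from crossover however costs are handled. Inflation of the ICER depends on the cost rule: it vanishes when joiners' costs are recorded by use and fall in proportion to benefit.

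**The case against.** Much of the concern rests on silence. A condensed article commonly leaves crossover handling to the full protocol or analysis plan, and the 12-month questionnaire (Appendix D) is not shown and may already ask about Scheme use. Self-directed follow-up is ordinary care for a comparison group, not an error. The Scheme operates in the private sector and private service use is surveyed in both groups, so some of a joiner's payments may be captured (k below 1). The co-payment phrase could even be read to include anyone who has joined. All of this stands, which is why the crossover rate and k are shown as ranges and the request is small. It does not answer the wording of the co-payment rule, which goes by group, or the fact that enrolment data not collected cannot be analysed.

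A reader might infer three stronger points that the article does not support:
- **That joiners' Scheme costs are loaded onto the CDCC group.** The per-participant division of Scheme costs is not stated. If it is made over all enrolees, a joiner's share is missing from the comparison group but is not added to the CDCC group.
- **That group membership is left open.** Subjects defines the intervention group by an enrolment window (1 January to 30 April 2024) and the comparators by recruitment. Status at recruitment is the natural reading.
- **That joiners would be deleted, biasing the result in the Scheme's favour.** No section provides for removal. The direction is also uncertain, because those with the worst values may be the likeliest to join and the least likely to reach target.

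**Conclusion.** The point holds in a limited form. Comparators are screened and prompted to act, the article states no barrier to joining the Scheme, and its co-payment rule goes by group label. Joiners would bring benefit into the comparison group without the matching cost. Both effects run against the Scheme: the attainment difference is understated and the ICER overstated.

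At an assumed 10–30% crossover with full benefit, 3 points becomes 2.7–2.1, and the ICER rises by up to 1.11–1.43 times. The upper figures need all of the joiners' Scheme cost to be missing. Late joining, partial benefit or partial capture of costs makes the effect smaller. Neither the crossover rate nor the capture of costs can be established from the article, so these figures show sensitivity and are not estimates of actual bias.

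**What to change.** 1. State that comparators are analysed in the group to which they were recruited, whether or not they later join the Scheme.
2. In the 12-month call, ask comparators whether and when they enrolled in the Scheme, unless the questionnaire already does so. Add a database look-up only where identifiers and consent allow; several extractions are described as anonymous, so linkage cannot be assumed.
3. Reword the cost rule so that Scheme co-payments and Scheme service costs follow actual use in either group. State how Scheme costs are divided per participant, and how Scheme use after the December 2024 cost cut-off is valued, since some comparator follow-up falls after that date.
4. Report the crossover proportion by diagnosis, with one simple sensitivity analysis by Scheme exposure. Censoring at enrolment with weights is not needed: outcomes are measured only at baseline and 12 months, so it would add little.

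**Cost.** One question in a call already planned and a short amendment. The as-recruited difference may be slightly smaller than one among comparators who never joined; reporting the crossover proportion lets readers judge by how much.
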